The second visit will involve a review of medication use and menstrual cycle details for female participants. The vital signs will be measured again, and participants will complete a series of questionnaires, including the Standard Tool for Pattern Identification of FD [2], Cold–Heat Pattern Questionnaire [26], Deficiency–Excess Pattern Questionnaire [27,28], Phlegm Pattern Questionnaire [29], Food Retention Questionnaire [30], Spleen Qi Deficiency Questionnaire [31,32], Stomach Qi Deficiency Questionnaire [33], Nepean Dyspepsia Index (NDI) [34], State-Trait Anxiety Inventory (STAI) [35], Beck Depression Inventory-II (BDI-II) [36], and the EeroQol-5-Dimension (EQ-5D) [37]. Participants may opt out of answering any questions they find uncomfortable. The Standard Tool for Pattern Identification of FD questionnaire comprises 45 items that categorize FD symptoms into six types: liver–stomach disharmony, dampness and heat in the spleen and stomach, spleen and stomach deficiency and cold, tangled cold and heat, food retention disorder, and insufficiency of stomach yin. This questionnaire demonstrates high reliability, indicated by its internal consistency, and a moderate level of validity, based on correlation analyses between the FD patterns identified by the tool, the Rome IV subtypes, and other dyspepsia-related questionnaires [2]. In addition, the Cold–Heat Pattern Questionnaire [26], Deficiency–Excess Pattern Questionnaire [27,28], Phlegm Pattern Questionnaire [29], Food Retention Questionnaire [30], Spleen Qi Deficiency Questionnaire [31,32], and Stomach Qi Deficiency Questionnaire [33] have been developed as pattern identification tools. These patterns are recognized as being significantly related to FD and the tools have been validated for both reliability and validity.

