### 2.7. Data Collection

Pattern identification will be conducted by licensed Korean medicine doctors via questioning, tongue diagnosis, pulse diagnosis, and abdominal diagnosis. This assessment determines deficiency–excess, cold–heat, and the presence of phlegm or food stagnation, as well as six primary FD differentiation patterns (spleen and stomach deficiency–cold, spleen Qi deficiency, liver–stomach disharmony, food stagnation, spleen deficiency with damp–heat, mixed cold and heat).

Bio-signal measurements will be conducted during the second visit or during the first visit only if the screening procedures confirm that the participants meet the inclusion criteria. Prefrontal cortex activity will be measured using a headband-type fNIRS device (NIRSIT; OBELAB Inc., Seoul, Republic of Korea). SCR, ECG, and pulse wave signals will be recorded with electrodes attached to the fingers, wrist, and chest, connected to the Biopac MP160 system (BIOPAC Systems Inc., Goleta, CA, USA). Radial artery pulse waves will also be measured using the DMP-LIFE PLUS pulse analyzer (DAEYOMEDI Co., Ltd., Ansan, Republic of Korea). These measurements will be conducted with the participants in supine position for two minutes. To maintain objectivity, the researcher measuring biometric signals will be different from the doctors diagnosing the patients with FD. Additionally, the diagnosis and pattern identification results will be blinded to both the researcher and the participants. Throughout the measurements, participants will be monitored thoroughly for any discomfort or adverse events.

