### 2.8. Statistical Analysis

Categorical variables include pattern identification results diagnosed by the Korean medicine doctors and those obtained from questionnaires for pattern identification. These variables will be used for subgroup analyses and as outcomes for AI-based prediction models, facilitating comparisons of differentiation patterns based on specific diagnostic results and bio-signals.

The questionnaire results of the NDI, STAI, BDI-II, and EQ-5D will be treated as numerical variables. The normality of the questionnaire results will be assessed to determine suitable statistical tests. Depending on normality, statistical tests like *t*-tests, analysis of variance, or non-parametric tests will be used to compare groups. Subgroup analyses will compare bio-signals between different diagnostic patterns. Correlation analyses will explore the relationships between the questionnaire results and categorical variables, while mediation and moderation analyses will assess potential factors that mediate or moderate the effects among the variables.

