For time-series bio-signals, various machine learning techniques have been shown to be effective in identifying spatiotemporal patterns for predictive and diagnostic tasks [39]. For single-channel signals, such as ECG or SCR, we plan to extract meaningful features that represent the physiological state or detect abnormalities using machine learning models, such as the random forest model. These features include traditional metrics (e.g., R-peak detection and morphological analysis) as well as advanced decomposition techniques (e.g., wavelet transforms and empirical mode decomposition) that facilitate the extraction of time–frequency domain characteristics to capture subtle and non-stationary signal behaviors [40]. Furthermore, deep learning-based methods, including 1D convolutional neural networks (CNNs) and transformer architectures, will be employed for automated and robust representation learning directly from raw signals.

For multi-channel signals, such as fNIRS or pulse wave data, we will utilize both linear and non-linear analytical methods to evaluate signal rhythms and variability. Recently introduced approaches (e.g., network analysis and attention-based models) allow for the modeling of long-term dependencies, revealing spatiotemporal patterns that traditional methods often fail to detect [41,42]. Graph-based models, such as graph neural networks and graph convolutional networks, show potential for analyzing inter-channel connectivity and exploring the functional relationships among multiple bio-signal sources [43]. By leveraging classical connectivity metrics, such as phase-locking values or mutual information, we expect these integrated approaches to yield more accurate and interpretable results.

To address potential confounding variables, we have identified key confounders such as variability in bio-signal measurements, subjectivity in diagnoses, and multi-collinearity among bio-signals. We will use multivariate regression and regularization techniques like Least Absolute Shrinkage and Selection Operator or ridge regression to handle multi-collinearity and apply principal component analysis for dimensionality reduction. Additionally, to ensure our models are based mainly on bio-signals, we will exclude questionnaire scores that strongly correlate with specific patterns. This approach helps maintain model robustness and aligns with our primary study objective.

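### The plan removes only strongly pattern-correlated questionnaire scores and tests only against chance, so an above-chance model would not show that bio-signals carry information

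*Protocol article*

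**What the plan says.** Four statements in the protocol article bear on this point.

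- **Outcomes (section 2.8).** "Categorical variables include pattern identification results diagnosed by the Korean medicine doctors and those obtained from questionnaires for pattern identification". These serve "as outcomes for AI-based prediction models" as well as for subgroup analyses.
- **Other questionnaires (section 2.8).** "The questionnaire results of the NDI, STAI, BDI-II, and EQ-5D will be treated as numerical variables".
- **Predictors (section 2.8, on confounding).** "to ensure our models are based mainly on bio-signals", the plan says, "we will exclude questionnaire scores that strongly correlate with specific patterns". It adds that this serves the primary objective.
- **Benchmark (end of section 2.8).** Classification accuracy and AUC, obtained by bootstrapping and cross-validation, are tested against chance levels of 0.5, 0.33 or 0.17 with a t-test at 0.05.

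Section 2.6 lists the instruments: seven for pattern identification, plus the NDI, STAI, BDI-II and EQ-5D. The Introduction gives the hypothesis that adding bio-signal data improves the accuracy with which patterns are predicted.

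**The concern.** The exclusion rule is meant to protect the study's claim that the bio-signals do the predicting. As worded it does so only in part. It removes a score when its correlation with the outcome is strong. A score with a weak or moderate correlation is not caught, and the stated goal is that bio-signals should dominate the model, not that they should be its only content. If no questionnaire score were a candidate predictor, the sentence would have no purpose.

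The benchmark does not repair this. Chance is what a model with no information achieves. A model with some questionnaire information and useless bio-signals also exceeds chance, and would be reported as a success of the bio-signal algorithm. The hypothesis in the Introduction concerns what bio-signals add, and a comparison with chance does not measure that.

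**Working it through.** **Plan's own figures.** Chance for k equally likely classes is 1/k: 1/2 = 0.50, 1/3 = 0.33, 1/6 = 0.17. These match section 2.8.

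**Inputs.** From the documents: 100 patients (section 2.3) and the chance level of 0.5 for a two-class outcome. Assumed: a balanced 50/50 pattern, the correlation r of each retained score with the pattern, the number of scores, and their inter-correlation ρ. The protocol supplies none of these. Section 2.6 credits the main pattern tool with "a moderate level of validity, based on correlation analyses between the FD patterns identified by the tool" and Rome IV subtypes and other dyspepsia questionnaires; that is not a correlation with the doctor's diagnosis. A range is therefore shown.

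**Step 1: what retained scores can do alone, in theory.** For a balanced binary outcome, a point-biserial correlation r gives a standardised difference d = 2r/√(1−r²). The best attainable accuracy is Φ(d/2), and AUC = Φ(d/√2). At r = 0.3, d = 0.6/√0.91 = 0.629, accuracy = Φ(0.314) = 0.62 and AUC = Φ(0.445) = 0.67. For k equally informative scores, d is multiplied by √(k/(1+(k−1)ρ)). With k = 5 and ρ = 0.3 the factor is √(5/2.2) = 1.51.

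| r | d | One score: accuracy | One score: AUC | Five scores: accuracy |
|---|---|---|---|---|
| 0.2 | 0.408 | 0.58 | 0.61 | 0.62 |
| 0.3 | 0.629 | 0.62 | 0.67 | 0.68 |
| 0.4 | 0.873 | 0.67 | 0.73 | 0.75 |
| 0.5 | 1.155 | 0.72 | 0.79 | 0.81 |

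No bio-signal information enters any of these figures.

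**Step 2: what survives the rule and cross-validation at n = 100.** Step 1 gives population optima, so a simulation was run with 1,000 data sets per setting. Each had 50 patients per class, five questionnaire scores (ρ = 0.3) and 10 or 20 bio-signal features of pure noise. Scores whose sample correlation with the pattern reached 0.5 (or, alternatively, 0.7) in absolute value were dropped. A ridge classifier was then assessed by 10-fold cross-validation. As a reference threshold, 59 or more correct out of 100 has probability 0.044 under chance. This is a binomial yardstick, not the plan's t-test.

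| r of each score | Scores kept (mean, of 5) | Cross-validated accuracy | Runs reaching 0.59 |
|---|---|---|---|
| 0.2 | 5.0 | 0.56-0.58 | 35-47% |
| 0.3 | 5.0 | 0.62-0.65 | 73-85% |
| 0.4 | 4.4-5.0 | 0.67-0.71 | 96-99% |
| No questionnaire scores | – | 0.50 | 7-10% |

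Ranges cover both cut-offs and both numbers of noise features. With r = 0, accuracy also stays at 0.50, so the excess comes from the questionnaire scores. The exclusion rule hardly acts: at these correlations nearly every score falls below either cut-off.

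**The case against.** The strongest reply is that the model inputs set out in section 2.8 are all bio-signals, and that the protocol nowhere lists a questionnaire score as a predictor. Instruments built to identify a pattern are the natural candidates for scores strongly correlated with patterns, so the rule may mean that they are removed as a class beforehand. This is fair, and it limits the point. It does not dispose of it: the NDI, STAI, BDI-II and EQ-5D would still not be excluded, and the same mechanism applies to them in so far as they correlate with a pattern. It may also be said that a combined model fits the hypothesis. That is true, but only if it is compared with a model without bio-signals.

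Four stronger readings are tempting, and the documents do not support them.

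- **Circularity.** A reader might infer that pattern questionnaires certainly remain as predictors of patterns that questionnaires define. No text says so, and the score defining an outcome would be the first that the rule removes.
- **Leakage through the filter.** A reader might object that no cut-off is given and that the filter is not tied to training folds. An article commonly leaves such detail to the full plan, and discarding the best correlates of the outcome does not itself inflate accuracy.
- **Unblinded doctors.** Section 2.7 says that "the diagnosis and pattern identification results will be blinded to both the researcher and the participants". It is silent on whether the doctors see questionnaire scores or device output, and silence does not show that they do. The same section has someone other than the diagnosing doctors take the measurements.
- **A larger effect.** If all seven pattern scores survived with r = 0.3-0.4 and ρ = 0.3-0.5, then R² = 7r²/(1+6ρ) = 0.16-0.40, equivalent to AUC 0.73-0.88. That supposes the rule removes nothing, that every instrument relates equally to one pattern, and that performance is optimal rather than cross-validated.

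**Conclusion.** The point holds in limited form. The rule as written allows questionnaire scores below a strong correlation to remain in models intended to show what bio-signals predict, and the stated test compares those models only with chance. If about five such scores remain, each correlating 0.3-0.4 with a balanced two-class pattern, they alone bring cross-validated accuracy to about 0.62-0.71 at n = 100; at 0.2 the figure is 0.56-0.58. An above-chance result could not then be credited to the bio-signals. The size rests on assumed correlations, number of scores and inter-correlation, and on some questionnaire scores being candidate predictors, which the wording implies but does not spell out. If none is in fact used, the problem disappears and only the sentence needs correcting. This is a cheap improvement to make before analysis, not a flaw that invalidates the study.

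**What to change.** Replace the correlation rule in section 2.8 with one fixed beforehand:

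1. The primary bio-signal model contains no questionnaire score. The seven pattern questionnaires are named and excluded for every outcome.
2. A questionnaire-only model and a combined model are fitted and assessed on the same cross-validation folds as the bio-signal model. For an outcome derived from a questionnaire, the instrument that defines it stays out of both, since it would otherwise predict itself.
3. The bio-signal contribution is judged by the increment in accuracy and AUC of the combined model over the questionnaire-only model, reported beside the bio-signal-only result. Comparison with chance alone is not taken as evidence for bio-signals.

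No extra patients, visits or measurements are needed. The cost is slightly more analysis, and the reported accuracy may be lower once questionnaire information leaves the primary model.

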## Abstract

**Background:** Functional dyspepsia (FD) is a common functional gastrointestinal disorder characterized by chronic digestive symptoms without identifiable structural abnormalities. FD affects approximately 8–46% of the population, leading to significant socioeconomic burdens due to reduced quality of life and productivity. Traditional medicine utilizes differential diagnosis through comprehensive examinations, which include observing and questioning, abdominal examination, and pulse diagnosis for functional gastrointestinal disorders. However, challenges persist in the standardization and objectivity of diagnostic protocols. **Methods:** This study aims to develop an artificial intelligence-based algorithm to predict identified patterns in patients with functional dyspepsia by integrating brain–body bio-signals, including brain activity measured by functional near-infrared spectroscopy, pulse wave, skin conductance response, and electrocardiography. We will conduct an observational cross-sectional study comprising 100 patients diagnosed according to the Rome IV criteria, collecting bio-signal data alongside differential diagnoses performed by licensed Korean medicine doctors. The study protocol was reviewed and approved by the Institutional Review Board of Kyung Hee University Hospital at Gangdong on 25 January 2024 (IRB no. KHNMCOH 2023-12-003-003) and was registered in the Korean Clinical Trial Registry (KCT0009275). **Results:** By creating AI algorithms based on bio-signals and integrating them into clinical practice, the objectivity and reliability of traditional diagnostics are expected to be enhanced. **Conclusions:** The integration of bio-signal analysis into the diagnostic process for patients with FD will improve clinical practices and support the broader acceptance of traditional-medicine diagnostic processes in healthcare.

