## 1. Introduction

Diagnosis and prognosis are critical parts of the medical process, with treatment and follow-up management strategies based on the diagnosis of a disease. In traditional medicine, such as traditional Chinese and Korean medicine, instead of identifying the disease itself, a pattern of symptoms is identified based on overall health conditions, including disease-related symptoms (e.g., gastrointestinal symptoms) and other lifestyle factors (e.g., working hours, sleep patterns, constitution, etc.) and subjective experiences that may not be detected by diagnostic medical devices (e.g., endoscopy, blood tests). This approach is known as the pattern identification method [1]. Based on the identified pattern, Korean medicine doctors prescribe herbal medicine, acupuncture, and manual therapies such as Chuna. Generally, Korean medicine is used primarily for musculoskeletal disorders, functional gastrointestinal disorders, and psychological conditions. In Korean medicine, functional dyspepsia (FD) is diagnosed using a technique involving four phases of examination: interview and observation, listening and smelling, questioning, and palpation. However, key diagnostic methods such as tongue diagnosis, pulse diagnosis, and abdominal diagnosis remain subjective and lack standardization. Recent advancements have included the development of standardized questionnaires to facilitate quantitative assessments for patterns, such as spleen and stomach deficiency–cold pattern, spleen and stomach damp–heat pattern, and food stagnation pattern in patients with FD [2]; However, diagnostic protocols used in clinics still heavily rely on these four examinations. Pulse diagnosis is a cornerstone in traditional medicine for determining conditions such as deficiency–excess (deficient or excessive energy level) and cold–heat patterns. For this examination, doctors continue to rely on their tactile perception, and various medical subdisciplines propose different methods for palpation and interpretation of these subjective sensations, leading to variability and challenges in objective assessments [3,4]. FD poses a significant challenge in healthcare due to its chronic nature and the lack of standardized, objective diagnostic tools. The diagnostic process remains largely reliant on the practitioner’s expertise and interpretation, leading to variability in diagnosis and treatment outcomes. Additionally, there is a critical gap in integrating objective, quantifiable data into the diagnostic process to enhance accuracy and consistency in the diagnosis of FD. Thus, a new approach is needed to address this gap by developing more comprehensive and data-driven diagnostic models.

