Additionally, we will investigate local and relative differences in brain activity through amplitude and frequency power analysis. Frequency-domain techniques (e.g., Fast Fourier Transform (FFT), Short Time Fourier Transform (STFT), and wavelet transforms) can be applied to extract spectral features from bio-signals, capturing power distributions across key frequency bands [44]. Recent hybrid approaches transform time-frequency representations into image-like inputs, enabling the use of CNN-based models to automatically discern frequency-related patterns. These methods can be used to enhance the sensitivity of diagnostic tools, particularly for complex and non-stationary bio-signals [45]. The significance and validity of the model will be assessed based on the classification accuracy and the area under the receiver operating characteristic (ROC) curve. These metrics will be obtained through bootstrapping and cross-validation methods and tested against a chance level (0.5, 0.33, or 0.17, depending on the prediction outcomes) using a *t*-test with a significance level of *p* < 0.05.

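### Chance is the only stated reference value for the model's validity; at n=100 about 59 to 61 right on a two-way label, or 24 to 26 on a six-way label, beats it and shows some signal but not useful or enhanced accuracy

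*Protocol article*

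**What the plan says.** In section 2.8 of the protocol article, "The significance and validity of the model will be assessed based on the classification accuracy" and the AUC. It continues: "These metrics will be obtained through bootstrapping and cross-validation methods", and they are "tested against a chance level (0.5, 0.33, or 0.17, depending on the prediction outcomes") by a t-test "with a significance level of *p* < 0.05". No minimum accuracy or AUC is given, and no comparator other than chance.

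The last paragraphs of the Introduction state the hypothesis in comparative terms: adding bio-signal data should raise the accuracy with which patterns are predicted. The Abstract goes further. In its Results, "the objectivity and reliability of traditional diagnostics are expected to be enhanced"; in its Conclusions, bio-signal analysis "will improve clinical practices and support the broader acceptance of traditional-medicine diagnostic processes in healthcare".

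The Introduction also says of current practice: "Recent advancements have included the development of standardized questionnaires to facilitate quantitative assessments for patterns". Section 2.6 and Table 1 schedule such questionnaires for every patient, including ones for cold–heat, deficiency–excess, phlegm and food retention. Section 2.7 has Korean medicine doctors label those same four axes, plus six main patterns. Section 2.8 uses the questionnaire patterns as subgroup variables and as prediction outcomes, not as a benchmark.

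**The concern.** Chance is a low reference for a diagnostic algorithm. A model can be clearly better than guessing and still disagree with the doctor in a large share of patients. If accuracy just above chance is reported under the label of validity, readers may take it as evidence that the algorithm can stand in for, or improve on, current diagnosis.

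A test against chance also cannot address the study's own hypothesis. A claim of enhanced accuracy needs something to be enhanced relative to, and a guess is not the current alternative. On four axes a current alternative, the pattern questionnaire, is completed by the same patients. The model could agree with the doctor less well than that questionnaire, and the analysis as described would not show it.

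**Working it through.** **Inputs.** N = 100 (2.3). Chance levels 0.5, 0.33 and 0.17, and significance level 0.05 (2.8). Sidedness is not stated, so both are shown.

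**The plan's own figures.** Chance = 1/k for k equally likely classes: 1/2 = 0.50, 1/3 = 0.33, 1/6 = 0.17. These match.

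**Pass marks under a correct test.** Find the smallest number correct r such that P(X ≥ r) is below 0.05 (one-sided) or below 0.025 (two-sided), with X ~ Binomial(100, p0).

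| Label | One-sided mark | Upper tail at the mark | Upper tail one below | Two-sided mark |
|---|---|---|---|---|
| Two-way, p0 = 0.5 | 59 | 0.044 | 0.067 | 61 |
| Three-way, p0 = 1/3 | 42 | 0.043 | 0.066 | 44 (43 with p0 = 0.33) |
| Six-way, p0 = 1/6 | 24 | 0.038 | 0.063 | 25 (26 with p0 = 0.17) |

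The one-sided marks do not pass two-sided: 59 against 0.5 gives p = 0.089, and 24 against 0.17 gives p = 0.082.

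**What the marks mean.** Errors are 100 − 59 = 41% to 100 − 61 = 39% for two classes, and 76% to 74% for six. With balanced classes, kappa = (accuracy − p0)/(1 − p0):
- two-way: (0.59 − 0.50)/0.50 = 0.18, and (0.61 − 0.50)/0.50 = 0.22;
- six-way: (0.24 − 0.167)/0.833 = 0.09, and (0.26 − 0.167)/0.833 = 0.11.

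**AUC.** With a 50/50 split (assumption), the null standard error is sqrt(101/(12 × 50 × 50)) = 0.058. The mark is 0.5 + 1.645 × 0.058 = 0.60 one-sided, or 0.5 + 1.96 × 0.058 = 0.61 two-sided.

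**The plan's own test.** It is a t-test on resampled metrics, and the number of folds or resamples is not stated. Assuming 10 folds of 10 patients, the two-way mark for mean accuracy is about 0.59 one-sided and 0.61 two-sided, much as above. Assuming bootstrap resamples with a standard deviation of 0.05, the two-sided mark is 0.510 with 100 resamples and 0.503 with 1000. The exact marks therefore do not exaggerate how low the bar is. Whether that t-test is sound is a separate question.

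**Which axes offer a benchmark.**
- Cold–heat, deficiency–excess, phlegm, and food stagnation/retention: both a doctor's label (2.7) and a questionnaire (2.6) exist.
- Six-way label: the questionnaire includes stomach yin insufficiency and no spleen Qi deficiency type. The doctors' list is the reverse, and the damp–heat names also differ. No direct comparison is possible without a mapping.

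**Precision of a paired comparison.** If 35% of patients are discordant, meaning that one method is right and the other wrong (assumption), the standard error of the accuracy difference is about sqrt(0.35/100) = 0.059. The 95% half-width is 1.96 × 0.059 = 0.116, about 12 points.

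**The case against.** Section 2.8 does not say that a model becomes valid once p falls below 0.05. A fair reading is that the t-test addresses significance while the size of accuracy and AUC informs validity. A reader might infer a written pass/fail rule, but the text does not contain one. What stands is narrower: chance is the only value the plan sets these metrics against.

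A performance threshold or a comparator may also be left to a fuller document. That is true of the details. But the article does fix a reference value, and it does not fit the comparative hypothesis or the Abstract's conclusions.

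The questionnaire is not a neutral benchmark. Doctors reach their label partly by questioning, so questionnaires share content with the reference in a way that bio-signals do not. Section 2.8 also keeps strongly correlated questionnaire scores out of the model on purpose. It is tempting to require the model to match the questionnaire before validity is claimed. The documents do not support that as a rule: no margin is given, no agreement figure for the questionnaires is reported, and a half-width of about 12 points could not settle it. These objections stand against a threshold, not against reporting the comparison.

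Finally, the Discussion calls the study an early step, and the Abstract's reliability wording is an expectation. That softens the tone but not the Abstract's firm statement about improving practice.

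**Conclusion.** The point holds as a matter of interpretation and reporting. At n = 100, beating chance corresponds to about 59 to 61 correct on a two-way label and 24 to 26 on a six-way label, with kappa near 0.2 and 0.1 respectively if classes are balanced. That is evidence of some signal. It is not evidence of useful validity or of enhanced predictive accuracy.

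The marks rest on an exact binomial test with all 100 patients analysed; the plan's own t-test could give lower ones. A reader might also infer that the questionnaires outperform the model. Nothing in the article shows that, because neither agreement rate is known yet.

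On reliability, Table 1 has one diagnosis visit and one bio-signal session, and no repeat assessment is described. The article does not say how many doctors assess each patient, so one cannot assert that each patient receives only one rating. It can be said that nothing described would support a reliability claim.

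**What to change.** 1. In 2.8, describe a significant result against the null as better than chance, and keep it apart from any statement about validity.
2. For cold–heat, deficiency–excess, phlegm and food stagnation/retention, report the model's out-of-fold accuracy and kappa against the doctor's label beside the questionnaire's accuracy and kappa against the same label. Add a paired patient-level bootstrap confidence interval for the difference. Present it as an estimate and not as a pass/fail rule, and note the content that questionnaires share with the doctor's questioning.
3. Do not use this benchmark where the questionnaire pattern is itself the outcome, or for the six-way label unless a mapping between the two lists is set out beforehand.
4. In the Abstract, limit the conclusions to internally validated agreement with the doctor's pattern label at one centre. Drop the reliability claim and the statement that practice will improve.

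Cost: a small extra analysis on data already scheduled, some rewording, and a less favourable headline.

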## 2. Methods

### 2.1. Study Design and Setting

This is an observational cross-sectional study combined with the development of an AI model. It will be conducted at Kyung Hee University Hospital in Gangdong, South Korea. Table 1 provides a summary of the study flowchart.

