### 2.3. Sample Size Calculation

Based on machine learning model requirements for predictive validity with categorical variables, a minimum of 50 samples per category is deemed necessary [22,23,24,25]. Considering potential variability and ensuring sufficient data for model training and validation, we aim to recruit 100 patients with FD.

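### The t-test of bootstrapped and cross-validated accuracy and AUC against chance makes no allowance for dependence between resamples of the same 100 patients, so the nominal 5% error rate does not hold

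*Protocol article*

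**What the plan says.** Section 2.1 describes one cohort: "This is an observational cross-sectional study combined with the development of an AI model". Section 2.3 sets its size: "we aim to recruit 100 patients with FD". Section 2.8 uses the doctors' pattern classifications and those from the questionnaires "as outcomes for AI-based prediction models".

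The success criterion is at the end of section 2.8. Significance and validity are "assessed based on the classification accuracy and the area under the receiver operating characteristic (ROC) curve". The text continues: "These metrics will be obtained through bootstrapping and cross-validation methods and tested against a chance level". The null values are given as "0.5, 0.33, or 0.17, depending on the prediction outcomes", and the comparison is made "using a *t*-test with a significance level of *p* < 0.05".

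The article does not state the number of folds, repeats or bootstrap samples, or whether the test is one- or two-sided. It mentions no permutation test, corrected variance or held-out test set.

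**The concern.** A one-sample t-test takes its values to be independent. Accuracies or AUCs from bootstrap samples or repeated cross-validation are recomputed from the same patients, with overlapping training sets and repeated use of the same test patients. Their spread shows how results vary from one resample to the next within this cohort. It does not show how the result would vary in another 100 patients.

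Dividing that spread by the square root of the number of resamples gives a standard error that more computing can make as small as one likes. A chance deviation from 0.5 that this cohort happens to show then becomes significant once enough resamples are run.

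This is the only test the article states of whether the algorithm performs better than chance. If its error rate is wrong, an uninformative model can be reported with a significant p-value.

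**Working it through.** **Inputs from the protocol article.** 100 patients (2.3); t-test at 0.05 (2.8); chance levels 0.5, 0.33 and 0.17 (2.8). The chance levels reproduce as 1/2, 1/3 and 1/6. The cohort size equals two categories at the stated minimum: "a minimum of 50 samples per category is deemed necessary", and 50 × 2 = 100. The plan's error rate is 5%, or 2.5% in the better-than-chance direction if the test is two-sided.

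**Assumptions, because the article does not give them.** Balanced classes, 5 to 20 features unrelated to the labels, a ridge linear classifier, and each fold or resample entering the t-test as one value.

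**Hand check, two-class accuracy.**

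- Sampling error with 100 independent predictions: √(0.25/100) = 0.050.
- Spread of one fold of 10 patients: √(0.25/10) = 0.158.
- Single 10-fold: t-test standard error 0.158/√10 = 0.050, the right order of magnitude.
- Ten repeats of 10-fold (100 values): 0.158/√100 = 0.0158, about a third of the real error.
- The two-sided test then rejects above 0.5 + 1.984 × 0.0158 = 0.531. An exact one-sided binomial test of 100 independent predictions needs at least 59 correct (error 0.044).
- With a true standard error of 0.050, the chance of passing 0.531 under no signal is P(Z > 0.0314/0.050) = P(Z > 0.627) = 0.27.

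A simulation of this case (600 data sets each with 5 and 20 features) gave a true standard deviation of the mean of 0.054-0.063 against an average t-test standard error of 0.015, and 32% of data sets were declared above chance. For single 10-fold the figures were 0.061-0.069 against 0.047, and 5-6%.

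**Error rates for a no-signal model, two classes** (600 to 1000 simulated trials per setting; ranges cover 5 and 20 features):

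| Resampling | Metric | One-sided 0.05 | Two-sided 0.05, above chance (nominal 0.025) |
|---|---|---|---|
| Single 5-/10-fold | accuracy | 0.083-0.097 | 0.045-0.058 |
| Single 5-/10-fold | AUC | 0.107-0.116 | 0.056-0.071 |
| 10 × 5-/10-fold | accuracy | 0.319-0.354 | 0.294-0.326 |
| 10 × 5-/10-fold | AUC | 0.350-0.396 | 0.324-0.355 |
| Bootstrap, 100 | accuracy | 0.257-0.301 | 0.238-0.287 |
| Bootstrap, 100 | AUC | 0.387-0.391 | 0.369-0.381 |
| Bootstrap, 1000 | accuracy | 0.322-0.372 | 0.315-0.364 |
| Bootstrap, 1000 | AUC | 0.447-0.450 | 0.444 |

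**More classes, accuracy, one-sided 0.05** (10 features, 600 trials):

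| Classes | Single 10-fold | 10 × 10-fold | Bootstrap, 200 |
|---|---|---|---|
| 3 | 0.093 | 0.358 | 0.310 |
| 6 | 0.038 | 0.257 | 0.105 |

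**Check of the remedies.**

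- A label-permutation test of mean 10-fold accuracy in two classes had error 0.047 (300 trials, 99 permutations each). Its simulation standard error is √(0.05 × 0.95/300) = 0.013, so this agrees with 0.05.
- The variance-corrected resampled t-test replaces s²/J by s²(1/J + test size/training size). For 10 × 10-fold that is s²(1/100 + 1/9) = 0.121 s² instead of 0.010 s², a standard error √12.1 = 3.5 times larger. Its one-sided error was 0.068, 0.057 and 0.018 for two, three and six classes.

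**The case against.** **The inflation depends on a number the article does not give.** This stands. A reader might take 30-45% as the plan's error rate, but the article does not support one fixed rate. A single cross-validation pass would inflate the error only modestly, and six-class accuracy is affected less than two-class accuracy. On the other side, section 2.8 names bootstrapping, which implies many resamples, and leaving the count open puts the p-value in the analyst's hands.

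**The standard error does depend on patients in unrepeated k-fold cross-validation.** This also stands: the test folds are disjoint, and the hand check gives √(0.25/n). The claim that more computing shrinks it applies to the bootstrap and to repeated cross-validation.

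**The unit of the t-test is inferred.** A corrected resampled t-test, or a t-test on the 100 pooled out-of-fold predictions (about 6% above chance in a null simulation), would also fit the word. But a t-test on the resampled metrics is the natural reading, and nothing in the text points to a correction. An analysis plan could add the resample count; the test itself is fixed here.

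**The estimates would expose a weak model.** In part. Among false positives in one null simulation, median accuracy was 0.53 (200 bootstraps) and 0.56 (10 × 10-fold), visibly near chance. The p-value would still mislead.

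**Multiplicity.** A reader might add that five doctor-assigned classifications and seven pattern questionnaires give 1 - 0.95^12 = 46% for at least one false positive. That assumes 12 independent outcomes, whereas these share patients and overlap in construct; counting only above-chance results gives 1 - 0.975^12 = 26%. Naming a primary outcome, metric and model-selection rule is commonly left to the analysis plan. It is no part of this point.

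**Conclusion.** Wrong as written, on its natural reading: the test in section 2.8 does not have a 5% error rate. With bootstrap or repeated cross-validation, a two-class model with no signal is declared better than chance about 25-45% of the time. One-sided at 0.05, the figure is about 31-36% for three-class accuracy and about 10-26% for six-class accuracy. With one unrepeated 5- or 10-fold pass in two classes it is about 5-7% above chance against a nominal 2.5%, or up to about 12% for a one-sided 0.05 test.

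These sizes rest on balanced classes, noise features, a ridge classifier and assumed resample counts. Other model families were not simulated. The direction of the defect does not depend on those choices when resamples are many, because the values share the same patients whatever the classifier. The documents do not support the stronger inference that every version of the planned analysis is severely inflated, or that no form of t-test could serve.

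**What to change.** Replace the uncorrected t-test in section 2.8 with a label-permutation test:

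- Permute the labels across patients and rerun the whole pipeline (feature selection, dimension reduction, tuning and model choice) inside the cross-validation.
- Take p = (1 + number of permuted values at or above the observed value)/(1 + B).
- Use about 1000 permutations for light models, and a smaller B, stated in advance, for deep models.

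Where permutation is too costly, a variance-corrected resampled t-test is an acceptable alternative; name the variance formula. State the number of folds, repeats or bootstrap samples and the sidedness in advance. Give confidence intervals for accuracy and AUC that treat patients, and not folds or resamples, as the independent unit.

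The change needs no further patients or measurements. It costs protocol or analysis-plan wording and computing time, which is substantial for the deep models, and the p-values will be less favourable.
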